### Data management and statistical analysis

A.Sample size selection

Studies of predictive model development indicate that is necessary to include at least 10 events of the dependent variable of interest (in this case: mortality, major complications, relapses or readmissions) for each independent variable included in the multivariate logistic regression model [31, 32]. Therefore, we estimated that at least 100 events of the dependent variable in the sample are required in order to ensure that the regression model would adequately converge. Previous data indicate that the number of events of the dependent variable mortality would be > 15 % of patients operated on in the first year, higher that the expected percentages of other parameters. We therefore estimated that more than 300 events of any of the dependent variables of interest should be included.

Sampling: we consecutively collected all new cases until the sample size was achieved.B.Missing data assumptions and recoding of variables

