Predictive models will be developed to address objectives 1 and 2. The overall sample will be randomly divided into derivation and validation sets. On the one hand, for binary outcomes (such as death, tumor recurrence, major complications, or readmission), multivariate hierarchical logistic models will be used. Goodness-of-fit of models will be assessed by means of the Hosmer–Lemeshow test (*p*-values > 0.05 indicate good model calibration) and the area under the Receiver Operating Curve (ROC), AUC, will be used to evaluate the discrimination ability of the final performance models. An AUC value > 0.80 will indicate that the model discriminates well. Furthermore, multivariate Cox regression models will be used to answer to those objectives. On the other hand, in cases of continuous outcomes (variables related to deterioration of quality of life) as with objective 3, the use of multivariate hierarchical linear mixed models is proposed. The intraclass correlation coefficient (ICC) will be calculated to assess the correlation among observations within a cluster by dividing the patient variance by the total sample variance. A small coefficient would indicate that patients and participant centers are independent.

For study endpoints related to health services research, the following statistical approaches will be used: for two-level outcomes, the Student’s t-distribution or the non-parametric Wilcoxon test (for non-normal distributions) will be applied. Where there are three or more categories in the outcome, ANOVA analysis or a Kruskal–Wallis approach (for non-normal distribution) are the proposed tests. Otherwise, for categorical variables, the Chi-square test (or Fisher’s Exact method, where required) will be used. Multivariate models will be used as needed for appropriate adjustments. For some analyses, subgroups based on tumor location (colon or rectum) will be identified.

An analysis of comparative costs between two alternative surgical approaches (open and laparoscopic surgery) will be performed. For this purpose, generalized linear models (GLM) will be employed using the patient level cost as the dependent variable and taking clinical covariates into account (age, sex, stage, among others). The statistical model will determine which covariates are associated with higher costs, as well as any significant differences in cost between the two alternatives. Analysis will be conducted at 2 and 5 years of follow up.

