## Discussion

As illustrated in Fig. 2, by the time of manuscript preparation, 2749 patients had been recruited according to the study protocol described previously, 1980 of which had been diagnosed with colon cancer and 769 with rectal cancer. This population represents a relatively large cohort of colorectal cancer patients for prospective follow up. Description of the basic characteristics of the sample, stratified by colon or rectal cancer diagnosis, is displayed in Table 2.

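### A non-significant Hosmer–Lemeshow test is read as good calibration, although in a validation subset it often misses moderate miscalibration, most of all for rarer endpoints

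*Protocol article*

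**What the plan says.** Part C (Statistical Analysis) of the protocol article's data management and statistics section covers objectives 1 and 2. It says that "for binary outcomes (such as death, tumor recurrence, major complications, or readmission), multivariate hierarchical logistic models will be used". On data use: "The overall sample will be randomly divided into derivation and validation sets"; the ratio is not given. On calibration: "Goodness-of-fit of models will be assessed by means of the Hosmer–Lemeshow test", followed by the interpretation that p-"values > 0.05 indicate good model calibration". Discrimination is judged separately by the AUC.

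The size of the information comes from two other places. The Discussion reports that "2749 patients had been recruited according to the study protocol described previously". Part A (sample size) expects that "mortality would be > 15 % of patients operated on in the first year", a rate it calls "higher that the expected percentages of other parameters", and concludes: "We therefore estimated that more than 300 events of any of the dependent variables of interest should be included". No rate is given for any endpoint other than mortality.

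**The concern.** The Hosmer–Lemeshow null hypothesis is that predicted and observed risks agree. Failing to reject it may mean that they agree, or that there were too few events to see that they do not. The article's interpretation merges the two. The p-value also gives neither the direction nor the size of any error in predicted risk.

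This matters because the section on expected outcomes wants simple rules on everyday devices and a medium-term prognosis for patients. For that use the predicted risk itself has to be about right; a good AUC shows only that patients are ranked well. Two features of the plan weaken the test further: splitting the cohort reduces the events available to it, and every endpoint except mortality is expected to be less frequent than mortality.

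**Working it through.** **Inputs from the article.** Cohort 2749; first-year mortality above 15%; other endpoints lower; more than 300 events planned; random derivation/validation split; threshold p > 0.05.

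**Assumptions.** Half split, 2749/2 ≈ 1375 in the validation set; 10 risk groups; 10 degrees of freedom, because the predictions are fixed before validation; independent patients (hospital clustering ignored); true linear predictor with SD 1; 5% (and 3%) as illustrative rates for rarer endpoints.

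**Step 1: the plan's event figure.** At 15%, 0.15 × 2749 = 412 events, so more than 300 holds for first-year mortality (300/0.15 = 2000 patients would be enough). Any other endpoint needs a rate of 300/2749 = 10.9%. The planned sample size and the other rates are not stated, so the figure can be checked only as an inequality. A half split leaves 1375 × 0.05 ≈ 69, 1375 × 0.109 ≈ 150 or 1375 × 0.15 ≈ 206 events for validation.

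**Step 2: the test.** The statistic is the sum over groups of (O − E)² / [E(1 − E/n)], where O, E and n are the group's observed events, expected events and size. A model passes if the statistic is below the 95th percentile of chi-square. The pass rate is 1 − power and was obtained by simulation. For slope 0.8 the predictions are spread 1/0.8 = 1.25 times too widely on the logit scale; 20% over-prediction means O/E = 1/1.2 = 0.83.

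**Step 3: pass rates, n = 1375, 10 df.**

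| Event rate | Events | Slope 0.8 | 20% over-prediction |
|---|---|---|---|
| 5% (assumed) | 69 | 72% | 94% |
| 10.9% (300 of 2749) | 150 | 61% | 75% |
| 15% | 206 | 55% | 57% |

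At 5% a perfectly calibrated model also passes about 94%, so there the test does not separate it from one that overstates risk by 20%.

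**Step 4: sensitivity.**
- Repeat simulations gave 69–72% for slope 0.8 at 5%. For 20% over-prediction at 15% they gave 50–57%; the value depends on whether every risk is multiplied by 1.2 or the intercept is shifted.
- With 8 df, pass rates are roughly 9 to 19 points lower. Part of that drop is excess rejection: in a separate simulation at 5% (n = 1374), a correctly calibrated model is rejected 12.5% of the time with 8 df against 6.1% with 10.
- Slope 0.7 passes 47% at 3%, 36% at 5% and 18% at about 11%. Risks overstated by a third (O/E 0.75) pass 19% at about 11%.
- With stronger predictors (AUC about 0.78–0.80, n = 1374), slope 0.7 passes 33%, 24%, 10% and 4% at 3%, 5%, 10% and 15%. Overstatement by a third passes 94%, 81%, 29% and 4%.
- If only a third of patients are held out (n = 916), overstatement by a third passes 57% at 10% and 21% at 15%.

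**Step 5: what an estimate would show.** An approximate 95% interval for O/E is the estimate divided and multiplied by exp(1.96 × √((1 − p)/events)). At 5% the factor is exp(1.96 × √(0.95/69)) = 1.26; at 15% it is exp(1.96 × √(0.85/206)) = 1.13. An observed O/E of 0.83 at 5% therefore has an interval from 0.83/1.26 = 0.66 to 0.83 × 1.26 = 1.05. The interval shows how little is known; p > 0.05 would be reported as good calibration.

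**The case against.** The other side has several fair points.

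- **Wording.** A reader might infer that the plan treats p > 0.05 as proof, or adopts and discards models on it. The article says only that such values indicate good calibration and ties no adoption decision to the result. That reading is dropped; the faulty interpretation remains.
- **Scope.** It would be too strong to say that badly calibrated models pass in general. A slope of 0.5 is rejected 90–97% of the time even at 2% events, and first-year mortality in a half sample gives good power against slope 0.7 or overstatement by a third.
- **Event rates.** The 3% and 5% rates are not in the article. If every endpoint reached 300 events, large errors would mostly be detected with a half split. Slope 0.8 would still pass about 61% and 20% over-prediction about 75%.
- **Common endpoints.** A reader might also expect the test to condemn frequent endpoints for small errors. The article gives no rate that supports this: part A puts mortality, above 15%, as the highest. Even at 35% events, slope 0.8 passes about 38% in 1375 patients.
- **Analysis set.** The article does not say where the test is run. In the derivation data, maximum likelihood in an ordinary logistic model forces slope 1 and agreement of mean risk, so the errors above concern validation. Power in derivation data against a moderate unmodelled curve is also low: 27–32% at 5% and 42–52% at 15% (8 df, n = 1374 to 1832).
- **Condensed article.** Not naming a calibration plot or slope is no fault here, since a fuller plan may contain them. The publication policy also commits to TRIPOD. Neither withdraws an interpretation that the article states outright.

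**Conclusion.** The point holds as a fault in a stated interpretation. Reading non-rejection as good calibration is unsound at any sample size. In a validation half of this cohort, moderate miscalibration passes more often than not: about 55–72% for slope 0.8 and 57–94% for 20% over-prediction, across event rates of 15% down to 5%. With 8 df the rates are lower but still substantial: about 45% and 55% at 10.9%. Larger errors escape often only at the assumed rates of 3–5%.

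The figures rest on an assumed half split, 10 groups, independent patients and a linear-predictor SD of 1. The direction does not: power falls with the number of events, so the interpretation is most lenient where there is least information. The flaw can be fully corrected at analysis and should be.

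**What to change.** Delete the statement that p > 0.05 indicates good calibration. For each binary model, report in the validation data calibration-in-the-large (or O/E) and the calibration slope, each with a 95% confidence interval, and a smoothed calibration plot. Judge calibration by the size of the estimates and the width of the intervals. Do not replace the p-value by asking whether the interval contains the ideal value: that is the same non-significance reasoning and again favours endpoints with few events. Hosmer–Lemeshow may stay as a supplementary result, with the analysis set, number of groups and degrees of freedom stated.

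The cost is a few lines of wording and standard output; no new data are needed. The downside is that some models, especially for rarer endpoints, can no longer be described as well calibrated.

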## Methods/design

### Study design

An observational analytic prospective cohort study with a planned patient follow up period of 5 years following surgical intervention.

Setting: patients recruited from 22 hospitals representing 9 provinces in Spain, all of which operate under the Spanish National Health Service (SNHS), which is responsible for the majority of the national population. All applicable residents have free access to their primary care physician and to the hospital ED. Participating hospitals are: Hospital de Antequera, Hospital Costa del Sol, Hospital Universitario de Valme, Hospital Universitario Virgen del Rocío, Hospital Universitario Virgen de las Nieves, Hospital Universitario de Canarias, Corporació Sanitaria Parc Taulí, Althaia, Hospital del Mar, Hospital Clínico San Carlos, Hospital Universitario La Paz, Hospital Infanta Sofía, Hospital Universitario Fundación Alcorcón, Hospital Galdakao-Usansolo, Hospital Universitario Araba, Hospital Universitario Basurto, Hospital Universitario Cruces, Hospital Hospitalario Donostia, Hospital Bidasoa, Hospital de Mendaro, Hospital de Zumarraga and Hospital Universitario Doctor Peset.

Research population: Patients diagnosed with colorectal cancer that underwent surgical intervention at one of the listed hospitals between June 2010 and December 2012. Patients were informed of the study objectives and invited to voluntarily participate. Patients were included in the study sequentially.

Expected duration of the study: patients will be followed until 5 years after the surgical index intervention, or until death.

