The Duke-UNC FSSQ questionnaire is composed of 11 items, each of which is rated on a five-point Likert scale ranging from 1 to 5: the higher the score, the better the perceived social support. It assesses subjective social support in two domains, Confidant support: 6 items (score range 6–30) and Affective support: 5 items (score range 5–25), and provides an overall social support measure (score range: 11–55) [27]. The questionnaire has been translated into and validated in Spanish [28].

The BI questionnaire consists of 10 items that assess the ability to perform certain basic activities of daily life without help. It includes 2- and 4-point response options that produce a score ranging from 0 (completely dependent) to 100 (completely independent), with intervals of 5 points [29]. The BI has been translated into and validated in Spanish [30].

Patients were first contacted upon inclusion in the surgical waiting list for a surgical intervention or were interviewed during their hospital admission period. Questionnaires were subsequently provided at 30 days, and at 1, 2, 3 and 5 years after surgery. In all instances, a reminder letter was sent to patients who had not replied after 15 days. Those who had not responded after a further 15 days received another reminder letter and, where feasible, contacted by telephone.

Questionnaires for the 30 day follow up visit were sent to patients attending the following hospitals: Hospital Costa del Sol, Hospital Valme, Hospital Virgen del Rocío, Hospital Virgen de las Nieves, Corporació Sanitaria Parc Taulí, Hospital Universitario La Paz, Hospital Infanta Sofía, Hospital Clínico San Carlos, Hospital Fundación Alcorcón, Hospital Basurto, Hospital Cruces, Hospital Donostia, Hospital Galdakao-Usansolo, Hospital Txagorritxu.

Figure 3 illustrates the data gathering process established for the entire follow-up period.

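### The intraclass correlation is defined with patient variance in the numerator but read as a measure of centre clustering, so the stated interpretation does not follow

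*Protocol article*

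**What the plan says.** In the protocol article, Data management and statistical analysis, part C (Statistical Analysis), the plan turns to continuous quality-of-life outcomes, as in objective 3, and says that "the use of multivariate hierarchical linear mixed models is proposed". It then introduces an ICC, which "will be calculated to assess the correlation among observations within a cluster". The formula and its reading follow in direct succession: the ICC is to be obtained "by dividing the patient variance by the total sample variance. A small coefficient would indicate that patients and participant centers are independent".

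Two features of the design determine what these sentences can mean. The Setting paragraph describes "patients recruited from 22 hospitals representing 9 provinces in Spain", so patients are nested in hospitals. The part of the data collection section on patient-reported outcomes says "Questionnaires were subsequently provided at 30 days, and at 1, 2, 3 and 5 years after surgery", so visits are nested in patients. The article does not say which of these levels is the cluster, and no other section restates or corrects the formula.

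**The concern.** An ICC describes how alike observations are when they share a cluster. Its numerator must therefore be the variance between the clusters in question. A statement about dependence on hospital needs between-hospital variance on top. The plan puts patient variance there and then draws a conclusion about hospitals.

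This is a positive statement in the article, not a detail left to a fuller document: both a formula and its reading are given. An analyst who follows the text would report one quantity and describe it as another. At stake is what the study reports about clustering in its 22 hospitals, which is of some interest in itself because objective 5 covers equity and access to care.

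**Working it through.** **Inputs.** The formula and its reading come from the Statistical Analysis part. There are 22 hospitals (Setting). The Discussion states that "2749 patients had been recruited according to the study protocol", and the 22 counts in Table 1 add up to that total, with a range of 28 to 332 and a mean of 2749 / 22 = 125.0. The article gives no ICC value and no variance component, so there is no figure of the plan's own to reproduce. All variance shares below are assumptions, chosen to show how the ratio behaves.

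Write Vc for between-centre variance, Vp for between-patient variance within centre, and Ve for visit-to-visit residual variance.

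**Step 1. Patients within centres, one observation each.** The total is Vc + Vp.

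- Plan's ratio: Vp / (Vc + Vp)
- Centre ICC: Vc / (Vc + Vp)
- The two add up to 1, so plan's ratio = 1 − centre ICC.

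| Assumed centre share | Plan's ratio | Centre ICC |
|---|---|---|
| 0 | 1.00 | 0 |
| 0.05 | 0.95 | 0.05 |
| 0.20 | 0.80 | 0.20 |
| 0.90 | 0.10 | 0.90 |

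The ratio is at its maximum when patients are independent of centre. It is small only when centres account for nearly all the variance. Under this model the plan's reading is reversed.

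A simulation with the 22 hospital sizes of Table 1 and analysis-of-variance estimates (500 runs per setting) agrees. For true centre shares of 0, 0.05 and 0.20, the plan's ratio averaged 1.000, 0.950 and 0.804, and the centre ICC averaged 0.000, 0.050 and 0.196.

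**Step 2. Visits within patients within centres.** The total is Vc + Vp + Ve, set to 1.

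- Plan's ratio: Vp / total
- Centre ICC: Vc / total
- Correlation between two visits of the same patient: (Vc + Vp) / total

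| Vc | Vp | Ve | Plan's ratio | Centre ICC | Same-patient correlation |
|---|---|---|---|---|---|
| 0 | 0.50 | 0.50 | 0.50 | 0 | 0.50 |
| 0.05 | 0.50 | 0.45 | 0.50 | 0.05 | 0.55 |
| 0.20 | 0.50 | 0.30 | 0.50 | 0.20 | 0.70 |
| 0 | 0.05 | 0.95 | 0.05 | 0 | 0.05 |
| 0.20 | 0.05 | 0.75 | 0.05 | 0.20 | 0.25 |
| 0.40 | 0.05 | 0.55 | 0.05 | 0.40 | 0.45 |

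The ratio does not move with the centre ICC. In the last three rows it is small at 0.05, which the plan would read as independence, while the centre ICC is 0, 0.20 or 0.40. Here the ratio carries no information about centres.

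**Step 3. Patient as the only random effect.** The formula is then the usual within-patient ICC and is correct as a formula. A small value would mean weak correlation between visits of one patient. Centre variance is not estimated in such a model. Any that exists is mixed into the patient term, so the ratio cannot show how much belongs to hospitals.

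**Step 4. Centre variance in the numerator.** The ratio is 0 when patients are independent of centre and rises with clustering, so the plan's interpretive sentence becomes correct.

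**The case against.** The strongest defence is that the formula may be right and only the last sentence misplaced. The ICC follows the models for objective 3, which concerns repeated patient-reported outcomes. With the patient as the cluster, patient variance over total variance is a standard coefficient. That is fair, and it means that the reversal in step 1 holds only under the patients-within-centres reading. It does not rescue the text, because the sentence about participating centres still has no support from that ratio.

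A second defence is that this is probably a slip, with patient written for centre, since that one change makes the formula and its reading agree. This is plausible and makes the repair small. The published wording still instructs the wrong calculation.

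A third defence is that nothing depends on the coefficient. This stands, and it limits the point. The plan proposes hierarchical models from the outset, sets no threshold for the ICC, and has no rule for dropping or keeping a hospital effect.

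A reader might nevertheless infer that standard errors will be wrong. With a mean of 125 patients per hospital and an assumed centre ICC of 0.05, the design effect would be 1 + (125 − 1) × 0.05 = 7.2; with an assumed 0.01 it would be about 2.2. The documents do not support carrying that over to this study. The figures apply to a hospital-level factor analysed with clustering ignored, the ICC values are assumed, and the plan does not say that it will ignore clustering on the strength of this coefficient.

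**Conclusion.** The point holds as a mismatch between a formula and its interpretation. None of the three structures examined makes the plan's ratio a measure of centre clustering. With patients nested in centres it is 1 minus the centre ICC (1.00 under independence, 0.95 at an assumed centre share of 0.05), so the reading is reversed. With repeated questionnaires and the patient as the cluster, it concerns within-patient correlation and does not measure dependence on centre.

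The algebra needs no assumption beyond additive variance components; only the illustrative shares are assumed. The consequence is a wrong reported coefficient and a wrong statement about clustering in the hospitals. It does not extend to the validity of the fitted models or their standard errors. The text should be fixed, but the error does not undermine the analysis strategy.

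**What to change.** Replace the formula and its reading in the Statistical Analysis part as follows:

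- Define the centre ICC as between-centre variance divided by total variance. Where visits are repeated, the total is centre + patient + residual variance.
- Attach the sentence about independence of patients and centres to that ratio only.
- If repeated questionnaires are modelled, report the within-patient correlation as a separate coefficient, (centre + patient variance) / total, and interpret it as similarity between visits of the same patient.

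The cost is one corrected formula and one or two sentences. No new data are needed, and the proposed class of models does not change.

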### Study goals and objectives

The purpose of this study is to clarify some of the previously stated questions and unknown factors. The specific study objectives are displayed in Fig. 1 and are: 1. To determine risk factors for death or major complications, reoperations, or readmissions in the short-term; 2. To determine risk factors for death, tumor recurrence, major complications, readmission or deterioration in quality of life in the mid-term; 3. to evaluate patient reported outcomes from before intervention to the end of the follow-up period. 4. To evaluate the role of biological markers in the prediction of adverse results; and 5. from a health services research perspective, to evaluate equity, appropriateness, access to care, treatment cost, and psychosocial support for patients.

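### Health-services comparisons and the cost model name no term for hospital, so contrasts that vary by hospital can be falsely significant; the test-selection rule is also misworded

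*Protocol article*

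**What the plan says.** Objective 5 (Study goals and objectives) is "to evaluate equity, appropriateness, access to care, treatment cost, and psychosocial support for patients". The data are "patients recruited from 22 hospitals representing 9 provinces in Spain", and Table 1 lists 28 to 332 patients per hospital in six autonomous communities.

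Under C. Statistical Analysis, binary outcomes for objectives 1 and 2 get hierarchical logistic models, quality-of-life outcomes get hierarchical linear mixed models, and an ICC is to be calculated. The next paragraph covers the health-services endpoints:

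- An outcome with two levels is to be compared by a t-test, or by Wilcoxon if it is not normal.
- For more levels the rule reads "Where there are three or more categories in the outcome, ANOVA analysis"; Kruskal–Wallis is its alternative if normality fails.
- Categorical variables are to be compared by chi-square or Fisher's exact test.
- "Multivariate models will be used as needed for appropriate adjustments".

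For open against laparoscopic surgery, "generalized linear models (GLM) will be employed using the patient level cost as the dependent variable". The covariates named there are age, sex and stage, with the list left open. This cost analysis is planned at 2 and 5 years.

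**The concern.** There are two separate points.

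1. **Clustering.** The plan recognises that patients cluster within hospitals for its other objectives, but the tests it names for objective 5 treat all 2749 patients as independent, and no hospital term is named for the cost model. Where the compared groups are hospitals or regions, or a patient factor whose frequency differs between hospitals, standard errors are too small. Chance differences between hospitals could then be reported as inequity or as a cost difference.

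2. **Wording of the rule.** It chooses the t-test or ANOVA by how many categories the outcome has. Those tests need a continuous outcome; the categories belong to the grouping factor. Read literally, a categorical outcome falls under two rules, and a continuous one such as patient-level cost has no test in this list. The article says it is meant as a reference for later papers, so the error could be carried forward.

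**Working it through.** **Inputs from the article.** The Table 1 community totals are 490 + 101 + 689 + 343 + 998 + 128 = 2749, matching the stated total, in 22 hospitals. No power or significance level is stated for the health-services tests.

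**Assumptions.** Two-sided 5% tests; hospital ICC of 0.01, 0.02 or 0.05 for the outcome (0.10 as an extreme); and, for surgical approach, a between-hospital spread in laparoscopy use. Table 2 gives only overall use (58.11%), not rates by hospital.

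**Formula for a factor fixed at hospital level.**
- Size-weighted cluster size m = Σn² / Σn = 498,843 / 2749 = 181.46.
- Design effect DE = 1 + (m − 1) × ICC.
- True type I error of the naive test = 2 × [1 − Φ(1.96 / √DE)].
- Effective sample size = 2749 / DE.

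| ICC | DE | Effective N | Type I error |
|---|---|---|---|
| 0.01 | 1 + 180.46 × 0.01 = 2.80 | 980 | 0.242 |
| 0.02 | 1 + 180.46 × 0.02 = 4.61 | 596 | 0.361 |
| 0.05 | 1 + 180.46 × 0.05 = 10.02 | 274 | 0.536 |

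Simulating a t-test on a hospital-level factor with the Table 1 sizes gives 0.243 at ICC 0.01 and 0.536 at 0.05, so the formula is adequate.

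**Simulation by type of contrast.** Continuous outcome, no true difference, Table 1 sizes. Ranges span repeated runs; a dash means not run.

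| Contrast | ICC 0.01 | ICC 0.02 | ICC 0.05 |
|---|---|---|---|
| ANOVA, six communities | 47–48% | 72–73% | 92–95% |
| País Vasco against the rest, t-test | 24–25% | 34–36% | 54–56% |
| Open vs laparoscopic, logit SD of use 0.5 | 6% | 7% | 11% |
| Open vs laparoscopic, logit SD of use 1 | 8–9% | 12–13% | 19–21% |
| Patient factor with its own hospital ICC of 0.05 | 5.1% | – | 9.6% |
| Patient factor spread evenly across hospitals | 5.2% | – | 4.8% |

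Controls at ICC 0 give about 5%. At ICC 0.10 the evenly spread factor still gives 4.4%, and the factor with its own ICC of 0.05 gives 14.3%. A wider spread in laparoscopy use (logit SD 1.5) gives 11%, 16% and 28% at the three ICCs. Adding a hospital effect to the open against laparoscopic comparison returns it to about 5% at every ICC.

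**The rule.** It has three branches: outcome with two levels (t/Wilcoxon), outcome with three or more categories (ANOVA/Kruskal–Wallis), and categorical variable (chi-square/Fisher). The first two are special cases of the third, and none is a continuous outcome. On a 0/1 outcome in a large sample, a t-test nearly equals a chi-square test, so the misassignment does not itself inflate type I error.

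**The case against.** - **Inflation is not general.** A reader might infer that the equity and access tests will be falsely significant. The documents do not support that. Objective 5 does not say which groups will be compared; age, sex and social factors fit as well as region, and factors spread evenly across hospitals show no inflation. This stands.
- **The largest figures concern contrasts the plan does not name.** Nothing commits to a test by community. This stands, and those figures are illustrations. The one contrast that is named, open against laparoscopic cost, has inflation from negligible to moderate, and that rests on assumed hospital variation.
- **No ICC is given.** Nor does any passage show that access or cost depends more on hospital than other outcomes do. This stands. Still, an ICC of 0.01, which many would call small, already gives 24% for a hospital-level factor, because the clusters are large.
- **Adjustment is foreseen and the covariate list is open.** This softens the point but does not settle it. The sentence says neither when such models apply nor that they are hierarchical, and adjusting for patient covariates does not correct standard errors for hospital clustering.
- **A condensed article may leave random effects to the full plan.** This is fair for the cost model taken alone. But the article does name hierarchical models for some objectives and independence tests for this one.
- **The outcome wording is a slip for grouping factor.** Probably so. It remains wrong as written, but one should not infer that it causes false significance.

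**Conclusion.** The point holds in limited form and should be corrected. Followed as written, the health-services tests and the cost model make no allowance for hospital, so comparisons that vary by hospital can be falsely significant. At a nominal 5% and assumed ICCs of 0.01 to 0.05, type I error is about 47–95% for an ANOVA across six communities and 24–56% for one community against the rest. For open against laparoscopic surgery it is about 5–21% if the logit SD of laparoscopy use is at most 1. The ICCs and the spread in laparoscopy use are assumptions. The simulations use all 22 hospitals and so do not describe the 5-year cost analysis, which follows 18. The test-selection rule is a separate wording error with no effect on type I error of its own.

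**What to change.** 1. Extend the hierarchical approach already planned to objective 5: linear or logistic mixed models with a hospital random intercept. For hospital- or region-level factors use between-hospital degrees of freedom, for example 22 − 6 = 16 for a comparison of the six communities.
2. Add a hospital effect to the cost model, with 22 hospitals at 2 years and 18 at 5 years. The 18 hold 2749 − (100 + 33 + 28 + 39) = 2549 of the recruited patients. State that surgical approach is then compared within hospitals, which is a different quantity from the crude cost difference.
3. Reword the rule by outcome scale: a continuous outcome across two groups (t/Wilcoxon) or three or more groups (ANOVA/Kruskal–Wallis), and a categorical outcome by chi-square/Fisher. Use these simple tests for description only.

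The cost is plan wording; hospital is already recorded. The downside is wider intervals for regional contrasts. Canarias and Valencia have one hospital each, so their community effect cannot be separated from that hospital's effect, and the plan should say so.
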